**Figure 2. F2:**
[figure not shown]
Flow diagram of enrollment of study participants.

### 2.9. Statistical considerations

#### 2.9.1. Sample size estimation.

The number of patients required for this trial was determined on the basis of the primary outcome of the clinical response rate. With an estimated clinical response rate of 56.6% in the control group, we calculated that 168 participants would be required for the trial to achieve 80% power (β = 0.2) to detect a 20% difference in a clinical response rate increase in the trial groups. The allocation ratio was 1:1, at a 2-sided overall significance level of 5% (α = 0.05). The test statistic used was the 2-sided Z-Test with unpooled variance. With an estimated follow-up loss of 20%, we aimed to recruit 105 participants per group, which was 210 participants in total.

#### 2.9.2. Statistical analysis plan.

A descriptive analysis of the baseline characteristics of the participants will be performed. Continuous variables will be presented as means and standard deviations; categorical variables will be presented as medians and interquartile ranges (lower and upper quartiles). The Kolmogorov–Smirnov test and histogram analyses will used to determine whether continuous variables are normally distributed. Levene’s test will used for the evaluation of homogeneity of variances. Two independent groups of parametric variables will be compared using a Student’s *t* test. For non-parametric variables, the Mann–Whitney *U* test will administered.

The principles of intention-to-treat analysis will be used. The primary analysis dataset was the intention-to-treat set. Both primary and secondary outcomes will be compared between the trial and control groups for the superiority of the trial group over the control group. For primary outcome comparisons of clinical efficacy, categorical data were analyzed by Chi-square or Fisher’s exact test, as appropriate. All trial results will be presented as a summary of the outcome measures, together with the estimated effect size and its confidence interval. All data analysis will be performed by using the IBM SPSS 26. The significance level are established at 2 sides 0.05, and the confidence interval limits at 95%.

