## 2. Methods

### 2.1. Objectives

This trial is aimed to evaluate the effectiveness of the ULTRA-EMS therapy device in preventing the recurrence of IUAs and improving reproductive outcomes after operative hysteroscopy.

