### 2.6. Outcome measures

#### 2.6.1. Primary outcome.

a) Improvement of IUAs

The primary outcome of our study was the clinical response rate. After 2 menstrual cycles of treatment (about 2 months), hysteroscopy was performed to evaluate the recovery of endometrial cavity function. According to the recovery status, the clinical outcomes were classified into 3 levels (cure, improvement, and failure). These 3 stages had different standards. The first is the cure: after intrauterine treatment, the size and shape of the uterine cavity were normal, and the uterine angle and tubal opening were normal. The second is the improvement: IUAs score decreased after treatment. The severity of adhesions according to the American Fertility Society (AFS) IUA 19 classification.^[20]^ The last is the failure: they were unchanged clinical symptoms and a massive IUA condition. Overall response rate = (cure + improvement)/total number of cases *100%.

b)IUA evaluations

Before treatment, we evaluated and scored the severity of adhesions according to the American Fertility Society (AFS) IUA 19 classification.^[20]^ One of 2 reproductive surgeons in our hospital performed all operative hysteroscopies using the same techniques. During the operative hysteroscopy, the doctors then did hysteroscopic adhesiolysis for patients. Scores of 1 to 4 represent mild adhesions, 5 to 8 points for moderate adhesions, and 9 to 12 points for severe adhesions. Table 2 shows the details of the evaluation of IUA.

**Table 2 T2:** Score assessment of intrauterine adhesion.

**Evaluation variable**	**Score**

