#### 2.6..2. Secondary outcomes.

a)Menstruation outcome

We assessed the amount of menstrual status according to Higham’s pictorial blood loss assessment chart.^[21]^ Methods: 240 mm sanitary napkins were uniformly used, and the blood penetration area of each piece of switched sanitary napkins was recorded. Mild: blood penetration area ≤ 1/3 of 1 point of the total area of the sanitary napkin. Moderate: the blood penetration area accounts for 1/3 to 3/5 of the 5 points of the entire sanitary napkin area. Severe: the bleeding area is basically 20 points of the entire sanitary napkin area. The size of the lost blood clot is 1 point for small blood clots < 1 coin; 5 points for large blood clots ≥ 1 coin. When blood clots could not represent blood loss, the percentage of the recorded blood volume was estimated for recording. The score, quantity and days of each sanitary napkin were filled in the sanitary napkin count and score table. Table 3 shows the menstrual blood loss record card. Menstrual blood loss score = (number of sanitary napkins with a large amount of blood-stained × 20) + (number of sanitary napkins with a medium amount of blood-stained × 5) + (number of sanitary napkins with a small amount of blood-stained × 1) + (number of blood clots < 1 coin × 1) + (blood clots ≥ 1 coin × 5). We recorded the menstrual status before and after 2 menstrual cycles of treatment.

**Table 3 T3:** Record card for menstrual blood loss and assessment time point.

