	**Menstrual cycle**						
**Blood staining level of sanitary napkin**	**1st day**	**2nd day**	**3rd day**	**4th day**	**5th day**	**6th day**	**7th day**
Severe							
Moderate							
Mild							
Blood clots < 1 coin							
Blood clots ≥ 1 coin							
Menstrual color							
Dysmenorrhea							

b)*Changes in 3-dimensional vaginal ultrasonography*

The changes in endometrial structure and hemodynamics before and after treatment will be evaluated in both groups. Vaginal 3-dimensional ultrasonography was performed by the same physician (attending and above grade) during ovulation before treatment (12 to 14 days before menstruation) and ovulation after the third course of treatment, mainly measuring endometrial type, endometrial thickness (ED), endometrial volume, endometrial classification (A, B, C), uterine artery blood flow (PI, RI, S/D, PS), endometrial vascular index (VI), blood flow index (FI), vascular blood flow index (VFI), and blood flow classification (I, II, and III).

c) *Pregnancy rates and pregnancy outcomes*

Pregnancy rate and pregnancy outcome would be follow-up at 2 and 6 months after operation in both groups. The purpose of the follow-up was to evaluate the long-term effectiveness of the electro-ultrasound device intreating IUAs. Researchers will pay close attention to the patient’s pregnancy during the follow-up period.

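### Section 2.9.2 tests every secondary outcome for superiority at two-sided 0.05 without stating its inferential status, which raises the chance of a false positive in the device's favour

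*Protocol article*

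**What the plan says.** Section 2.6.1 names one primary outcome: "The primary outcome of our study was the clinical response rate". The sample size in 2.9.1 rests on it alone.

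The section on secondary outcomes has three items:

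- **a) Menstruation**, scored on a blood-loss chart: "We recorded the menstrual status before and after 2 menstrual cycles of treatment".
- **b) Three-dimensional ultrasound**: "mainly measuring endometrial type, endometrial thickness (ED), endometrial volume, endometrial classification (A, B, C), uterine artery blood flow (PI, RI, S/D, PS"), followed by "endometrial vascular index (VI), blood flow index (FI), vascular blood flow index (VFI), and blood flow classification (I, II, and III").
- **c) Pregnancy**: "Pregnancy rate and pregnancy outcome would be follow-up at 2 and 6 months after operation in both groups".

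Section 2.9.2 then puts primary and secondary outcomes under one rule: "Both primary and secondary outcomes will be compared between the trial and control groups for the superiority of the trial group over the control group". It adds one threshold: "The significance level are established at 2 sides 0.05, and the confidence interval limits at 95" per cent. It also promises an effect size with a confidence interval for all results. The article contains no testing order, no split of alpha, no dependence on the primary result and no supportive or exploratory label.

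The objective in 2.1 is to "evaluate the effectiveness of the ULTRA-EMS therapy device in preventing the recurrence of IUAs and improving reproductive outcomes after operative hysteroscopy".

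**The concern.** One named primary outcome needs no adjustment. The difficulty is that 2.9.2 gives the secondary outcomes the same superiority comparison and the same threshold as the primary, and nothing ties them to the primary result. As written, the plan does not prevent a superiority statement on a secondary measure after a null primary result.

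This matters because the objective has two halves. The primary outcome is a hysteroscopic response and speaks to recurrence of adhesions. The reproductive half can be answered only from secondary outcomes. Item c says that its follow-up is meant to assess how well the device works in the longer term. A reader of the results could therefore meet an effectiveness claim, backed by a superiority test at 0.05, that comes from a large set of measures with no error control across the set.

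**Working it through.** **The plan's own figure.** Inputs from 2.9.1: control response 56.6%, difference 20 percentage points (so 76.6%), 80% power, two-sided 0.05, unpooled Z-test, 20% loss.

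- n per arm = (1.960 + 0.842)² × (0.566 × 0.434 + 0.766 × 0.234) / 0.20² = 83.4, rounded up to 84, so 168 in total.
- 168 / 0.80 = 210.

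Both stated figures reproduce, so the primary analysis is sized consistently with the level in 2.9.2. The article states no error rate for the secondary outcomes as a set, so there is no such figure to reproduce.

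**Counting the secondary tests.**

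- Item a: 1 (blood-loss score).
- Item b: 12 (endometrial type, thickness, volume, A/B/C classification; PI, RI, S/D, PS; VI, FI, VFI, flow classification).
- Item c: 2 comparisons.
- Total: 1 + 12 + 2 = 15.

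The count falls to 14 if endometrial type and A/B/C classification are the same variable. It rises to 17 if pregnancy rate and pregnancy outcome are each tested at both 2 and 6 months.

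**Chance of a false result favouring the device.** Assume no true effect on any secondary outcome. A two-sided test at 0.05 gives a significant result in the device's favour with probability 0.025.

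- Independent tests: 1 − 0.975^k.
  - k = 15: 1 − 0.975^15 = 31.6%.
  - k = 14: 29.8%; k = 17: 35.0%.
  - k = 3: 1 − 0.975^3 = 7.3%.
- Correlated tests, with a common correlation ρ between normal test statistics: 1 − ∫ φ(x) · Φ((1.96 − √ρ·x)/√(1 − ρ))^k dx. The values of ρ are assumed.

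| Assumed ρ | 15 tests, device favoured | 15 tests, either direction | 3 tests, device favoured |
|---|---|---|---|
| 0 | 31.6% | 53.7% | 7.3% |
| 0.3 | 23.5% | 45.7% | 6.8% |
| 0.5 | 18.1% | 36.1% | 6.3% |
| 0.8 | 10.1% | 20.2% | 4.9% |

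For a single test, the corresponding figures are 2.5% (device favoured) and 5% (either direction).

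The independence row is an upper bound within this range rather than a realistic case. PI, RI and S/D describe the same artery flow, and VI, FI and VFI the same endometrial vascular assessment, so they will move together.

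**The case against.** **The article is condensed.** Handling of multiplicity for secondary outcomes is commonly left to a full analysis plan, which is not shown. Silence on it would be no finding. That stands as far as it goes, but 2.9.2 is not silent: it states the scope of the superiority comparisons and one level for them. An unseen plan that added a hierarchy or a label would be qualifying an unqualified published statement.

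**The labels already rank the outcomes.** They are called primary and secondary, the trial is sized on the primary alone, and the primary has its own test sentence. The superiority wording could simply name the type of comparison. Nothing says that a significant secondary result would carry a device claim by itself. This is fair: the article leaves that use open and does not announce it. Given the objective in 2.1, the opening still needs closing.

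**The count of 15 is a reading.** The article lists three secondary items and does not say that each ultrasound measure gets its own superiority test. This stands, and it is why the three-test figure of 5% to 7% is given beside the larger one.

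**Stronger readings that the documents do not support.**

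- A reader might infer that a false claim of device benefit is likely. The only figure above one half (53.7%) counts results in either direction and assumes independence. In the device's favour the range for 15 tests is 10% to 32%.
- A reader might compare the either-direction figures with a promised 5% for the whole set. The article makes no such promise. The overall 5% level in 2.9.1 belongs to the primary sample size.

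**Confidence intervals are already promised.** They are, and that supplies part of the remedy. It does not withdraw the superiority comparisons.

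**Conclusion.** The point holds as a matter of how 2.9.2 is worded. It places primary and secondary outcomes under one superiority rule at one level, with no order or supportive status, while half of the objective depends on the secondary outcomes alone.

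The inflation is about sevenfold in the central case: 18.1% / 2.5% = 7.2, for 15 separate tests at ρ = 0.5. It runs from about four times (10.1% / 2.5%) at ρ = 0.8 to almost thirteen times (31.6% / 2.5%) under independence. With only three tests it is about two to three times.

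These figures rest on three assumptions: no true effect on any secondary outcome, a common correlation that the documents do not give, and, for the larger figures, a separate test of each listed measure. The validity of the primary test is not in question. The change is worth making because it alters what the trial may conclude at almost no cost.

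**What to change.** In 2.9.2, replace the joint superiority sentence with wording such as: *Superiority will be concluded only from the clinical response rate, tested at two-sided 0.05. Secondary outcomes are supportive and will be reported as effect estimates with 95% confidence intervals, without claims of superiority.*

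If the sponsor wants a confirmatory claim on reproductive outcomes, it should prespecify a short fixed sequence before the data are unmasked. Each step would be tested at two-sided 0.05 only if the primary result and every earlier step are significant. The choice and order of outcomes are the sponsor's; nothing in the article dictates them. Measures outside the sequence stay supportive.

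The cost is a few sentences, with no extra patients, visits or data. The downside is that an isolated p<0.05 on a secondary measure can no longer be presented as proof of superiority.

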## 1. Introduction

Intrauterine adhesions (IUAs) were first reported by Fritsch in 1894.^[1]^ In 1950, Asherman systematically and comprehensively reported IUA through a summary of 29 IUA cases, so that people began to pay attention to and deeply studied this disease. Also, the IUAs is also known as Asherman syndrome.^[2]^ It is characterized by varying degrees of scar formation in the uterine cavity and is also the cause of menstrual disorders, infertility, and placental abnormalities.^[3,4]^ IUA occurs most often after infection or trauma, such as uterine surgery, especially in the postpartum period of cesarean section.^[5,6]^ A large number of inflammatory chemokines, together with cytokines and cell adhesion molecules, are aberrantly expressed during the development of IUA.^[7]^ The current report found that IUA was associated with decline in reproductive clinical outcomes after natural conception and assisted reproductive technologies.^[8]^ The prevalence of IUAs is currently not entirely consistent, ranging from 0.3% (an incidental finding in women with intrauterine device placement without gynecological symptoms) to 21.5% (women with postpartum curettage).^[9]^ Of all the tools used to diagnose IUA or evaluate the severity of IUA, hysteroscopy is the current gold.^[10]^ In the treatment, the recovery of uterine shape and function is mainly helped by surgical separation of the adherent uterine cavity, supplemented by physical isolation and hormone to promote endometrial regeneration.^[8]^ Operative hysteroscopy is also considered a good treatment for patients.^[11]^ The postoperative effectiveness of hysteroscopic separation of IUAs is generally satisfactory, and the probability of usual or improved menstruation after surgery can reach 92% to 96%.^[12]^ Recurrence of postoperative adhesions is one of the most important factors for poor reproductive outcome after operative hysteroscopy, especially in cases diagnosed with severe AS, where the recurrence rate is significantly higher.^[13]^ More and more scholars have focused on exploring the measures to prevent adhesion recurrence and improve postoperative pregnancy rate during and after operative hysteroscopy.^[10]^

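### Only unadjusted tests are named although baseline values are collected; adjusting for them would gain precision at almost no cost, most clearly for the continuous secondary outcomes

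*Protocol article*

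**What the plan says.** Section 2.9.2 of the protocol article gives the primary rule: "For primary outcome comparisons of clinical efficacy, categorical data were analyzed by Chi-square", or by Fisher's exact test where appropriate. For continuous variables, "Two independent groups of parametric variables will be compared using" a Student's t test, with Mann-Whitney as the alternative. Kolmogorov-Smirnov tests, histograms and Levene's test guide the choice. No covariate, stratified test or baseline-adjusted model is named. The section does not say whether the t or Mann-Whitney test is applied to follow-up values or to changes.

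Baseline information is collected:

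- Section 2.6.1(b) scores AFS severity before treatment as mild, moderate or severe.
- Section 2.6.2(a), on menstrual blood loss: "We recorded the menstrual status before and after 2 menstrual cycles of treatment".
- Section 2.6.2(b), on ultrasound: "The changes in endometrial structure and hemodynamics before and after treatment will be evaluated in both groups".

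Section 2.4 randomises in blocks of 4 and names no stratification factor. The Introduction says that recurrence after surgery is a main cause of poor outcome, "especially in cases diagnosed with severe AS, where the recurrence rate is significantly higher".

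**The concern.** When an outcome is measured before and after treatment, part of its spread at follow-up is predictable from the baseline value. A two-sample test on follow-up values leaves that part in the error term, and a test on changes removes it imperfectly. ANCOVA removes it with the best-fitting weight. At stake are confidence intervals wider than they need be for blood-loss score, endometrial thickness and volume, and the flow indices.

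The normality-check rule adds a second problem. It lets the data decide whether means or ranks are compared, and a Mann-Whitney test alone does not supply the effect estimate and interval that Section 2.9.2 promises for all results.

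The same reasoning applies to the binary primary outcome if baseline severity predicts response. Severity is neither a stated stratification factor nor a term in the test.

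**Working it through.** **1. The plan's own figure.** Section 2.9.1 gives these inputs: "With an estimated clinical response rate of 56.6% in the control group", a 20-point increase ("to detect a 20% difference in a clinical response rate increase in the trial groups"), 80% power, two-sided 5%, 1:1 allocation and an unpooled Z test.

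- Variance term: 0.566 × 0.434 + 0.766 × 0.234 = 0.4249.
- n per group = (1.960 + 0.842)² × 0.4249 / 0.20² = 83.4, so 84 per group and 168 in total.
- Allowing for 20% loss: 168 / 0.80 = 210.

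Both stated totals reproduce. Power at 84 per group is 80.3% with unpooled variance and 79.0% with the pooled variance of the chi-square test. The trial was therefore sized for an unadjusted comparison.

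**2. Continuous secondary outcomes.** Let ρ be the baseline/follow-up correlation within arm, and take equal variances at the two times. The documents give no ρ, so 0.3 to 0.7 is assumed. Relative variances of the treatment contrast are 1 for follow-up only, 2(1 − ρ) for change scores, and 1 − ρ² for ANCOVA. The ratio of ANCOVA to change is (1 + ρ)/2.

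| ρ | Change | ANCOVA | Cut vs follow-up only | Cut vs change |
|---|---|---|---|---|
| 0.3 | 1.40 | 0.91 | 9% | 35% |
| 0.5 | 1.00 | 0.75 | 25% | 25% |
| 0.7 | 0.60 | 0.51 | 49% | 15% |

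Take the effect that a follow-up-only comparison would detect with 80% power at 84 per group: (1.960 + 0.842) × √(2/84) = 0.43 SD. ANCOVA has 84%, 90% and 98% power for it at ρ = 0.3, 0.5 and 0.7. Change scores have 66%, 80% and 95%.

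**3. Primary outcome, by formula.** Suppose the baseline score explains a share R² of the variance in response. The documents give no R², so it is assumed. The variance of the adjusted risk difference is then multiplied by (1 − R²). At 84 per group:

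| R² | Power | 95% CI half-width (points) |
|---|---|---|
| 0 | 80.3% | 13.9 |
| 0.05 | 82.3% | 13.6 |
| 0.10 | 84.2% | 13.2 |
| 0.20 | 88.2% | 12.5 |
| 0.30 | 91.9% | 11.7 |

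**4. Primary outcome, by simulation.** There were 5,000 trials per setting with 84 per group, a normally distributed severity score, a log-linear relation to the odds of response, and marginal rates held at 56.6% and 76.6%. The adjusted risk difference came from a linear model with robust standard errors, as a stand-in for the standardised logistic estimate.

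| OR per SD of severity | Chi-square | Adjusted |
|---|---|---|
| 1.0 (not prognostic) | 78.7% | 78.9% |
| 1.65 | 79.8% | 81.4% |
| 2.23 | 80.1% | 84.2% |
| 3.32 | 79.8% | 87.6% |
| 4.95 | 79.6% | 90.1% |

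With no treatment effect, both methods rejected in about 5% of trials (4.7% to 5.3%). An uninformative baseline thus costs essentially nothing, and the larger gains need a strong relation.

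**The case against.** The strongest reply is that nothing here is an error. Chi-square or Fisher is valid for a 1:1 randomised binary outcome, and it is the kind of test the trial was sized for. Its type I error already allows for chance imbalance in severity. A fuller analysis plan, not shown, could add adjustment. All of this stands, and it limits the point to efficiency.

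Four stronger readings are tempting, and the documents do not support them.

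- **Baseline values are ignored.** They are not. Section 2.6.1(a) defines improvement as a fall in the adhesion score, and Section 2.6.2(b) speaks of changes, so ultrasound may be analysed as change. What is absent is covariate adjustment.
- **Severity is a known strong predictor of this outcome.** The Introduction's statement concerns recurrence, whereas the primary outcome is cure or any fall in score. A high baseline score has more room to fall, and a low one is closer to cure. The relation could run either way, be non-monotone, or be near zero.
- **The trial has no margin.** The 210 includes a 20% loss allowance. If all 105 per group were evaluable, unadjusted power would be 88% by the unpooled formula.
- **Surgeon is available as a covariate.** Section 2.6.1(b) says that one of two surgeons operated. It does not say that the operator is recorded in the data.

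The objection does not reach the continuous secondary outcomes. Whichever of follow-up values or changes is meant, ANCOVA is more efficient at every correlation in the assumed range.

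**Conclusion.** The point holds as an efficiency improvement, not as a fault in the test or the sample size. For continuous before/after outcomes, ANCOVA would cut variance by 9% to 49% against follow-up values, or by 35% to 15% against change scores, as the assumed correlation goes from 0.3 to 0.7. For the primary outcome the gain depends on an unknown prognostic strength. It is none if baseline AFS does not predict response, about 0 to 4 points of power if the relation is weak to moderate, and about 8 to 12 points if it is strong. The top of that range corresponds to an assumed R² of 0.30 and should not be read as an expectation. A reader might infer that the planned analysis is underpowered. It is not: it keeps its planned power of about 80%, and any loss is relative to the adjusted alternative.

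**What to change.** Before unmasking, amend Section 2.9.2 as follows.

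- **Continuous before/after secondary outcomes** (blood-loss score, endometrial thickness and volume, flow indices): use ANCOVA of the follow-up value on arm and baseline value, and report the adjusted difference with its 95% CI. Log-transform skewed measures. The blood-loss score can be zero, so state in advance how zeros are handled. This replaces the rule that chooses between t test and Mann-Whitney from normality checks.
- **Primary outcome:** use logistic regression of response on arm and baseline AFS score, reported as a standardised risk difference with 95% CI. This stays on the scale used for sizing. Fix the form of the AFS term in advance, because the relation may not be linear. Keep the chi-square or Fisher test as supportive.
- **Surgeon:** add it to the primary model only if it is recorded for each woman.

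The cost is a change of wording, with no new visits, patients or measurements. ANCOVA and logistic regression are routine in the named software; the standardised risk difference may need a short extra step. Adopted after unmasking, the same change would look data-driven.
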